**Methods/Design:**

This paper describes the research design of a large scale evaluation of the effectiveness of the Welsh Assembly Government's Primary School Free Breakfast Initiative. A cluster randomised trial, with school as the unit of randomisation was used for the outcome evaluation, with a nested qualitative process evaluation. Quantitative outcome measures included dietary habits, attitudes, cognitive function, classroom behaviour, and school attendance. The study recruited 111 primary schools in Wales, of which 56 were randomly assigned to control condition and 55 to intervention. Participants were Year 5 and 6 students (aged 9–11 years) in these schools. Data were collected for all 111 schools at each of three time points: baseline, 4 month and 12 month follow-up. This was achieved through a repeated cross-sectional survey of approximately 4350 students on each of these occasions. Of those students in Year 5 at baseline, 1975 provided data at one or both of the follow-ups, forming a nested cohort. The evaluation also included a nested process evaluation, using questionnaires, semi-structured interviews and case studies with students, school staff, and local authority scheme coordinators as key informants.

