### Statistical analyses

There was no one primary outcome, but a pre-specified analysis plan was agreed in which the following were identified as primary outcomes: the proportion of students consuming two breakfasts over two days; episodic memory; number of healthy food items consumed at breakfast and number of unhealthy food items consumed at breakfast according to the dietary recall questionnaire. Secondary outcomes were identified as attitudes towards eating breakfast; rest of day healthy food items; rest of day unhealthy food items; scores on the hyperactivity/inattention scale of the strength and difficulties questionnaire, and parental reports of frequency of eating breakfast at home and at school. A number of other outcome measures were *a priori *defined as tertiary outcomes, including cognitive measures other than episodic memory, the total difficulties score on the strengths and difficulties questionnaire, parental reports of morning routines and child care arrangements before school and variables collected from the individually administered in-depth dietary recall and cognitive measure interviews.

For each outcome variable, the primary analysis is a school-level weighted regression analysis [44] adjusting for baseline score and the four stratification variables. These primary analyses will be conducted on an intention-to-treat basis, in which each school is coded according to the treatment condition to which it has been randomised. A secondary analysis conducted for all variables will be a per protocol analysis, in which schools are coded according to whether or not a free breakfast scheme was set up prior to outcome measurement.

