### Participation rates and school attrition

Of the schools where baseline data were collected, no schools withdrew from the study prior to final data collection. There were however five schools randomised to the control group who nevertheless set up a free breakfast scheme prior to the 12-month follow up, while ten schools randomised to the intervention group had not set up the scheme within the follow-up period. Thus the per protocol analyses have 61 schools coded as control schools and 50 as intervention.

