### Attrition

Whilst issues surrounding attrition may arise from the relationship developed between schools and the research team, in the context of evaluating an initiative such as this one, where schools are asked to relinquish control of start dates for an otherwise available initiative, external pressures and difficulties may arise for schools at a later date which influence their ability to fulfil these obligations. These need to be dealt with sensitively on a one-to-one basis.

Whilst no schools refused to allow researchers into the school to collect all three rounds of data, a number of intervention schools experienced significant difficulties in setting up the scheme and ten were unable to set-up prior to follow-up data collections. All LEAs were informed which schools were in the control condition and were advised that these schools had agreed not to set up until after 12 month follow up. However, a number of control schools experienced external pressures from parents and other sources to set up the scheme earlier than agreed, which they felt unable to resist. In these instances, the research team attempted to either negotiate with schools to wait until the agreed date, or if such an agreement could not be reached, data collections were brought forward to a slightly earlier date to allow set up to take place earlier. In five cases, schools set up the scheme before these measures could be put in place. Data were still collected from all schools thus allowing intention to treat and per protocol analyses to be undertaken.

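### The secondary analysis called 'per protocol' is an as-treated comparison that moves 15 of 111 schools to the other arm, so it is non-randomised and open to confounding even after adjustment

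*Protocol article*

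**What the plan says.** The Statistical analyses section makes intention to treat primary: "each school is coded according to the treatment condition to which it has been randomised". The model is a weighted school-level regression with baseline score and the four stratification variables as covariates. The section then adds: "A secondary analysis conducted for all variables will be a per protocol analysis". The coding rule given for this analysis is that "schools are coded according to whether or not a free breakfast scheme was set up prior to outcome measurement".

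Participation rates and school attrition gives the result of that rule. On the control side it reports "five schools randomised to the control group who nevertheless set up a free breakfast scheme prior to the 12-month follow up". On the intervention side it reports that "ten schools randomised to the intervention group had not set up the scheme within the follow-up period". The resulting tally is stated as follows: "Thus the per protocol analyses have 61 schools coded as control schools and 50 as intervention". The abstract gives the randomised numbers: 111 schools, "of which 56 were randomly assigned to control condition and 55 to intervention".

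The Attrition section of the Discussion gives the reasons. Some intervention schools met serious difficulties in setting up, and "a number of control schools experienced external pressures from parents and other sources to set up the scheme earlier than agreed".

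**The concern.** A per-protocol analysis normally drops units that departed from their allocation. This rule keeps every school and reassigns the departing ones to the arm whose behaviour they matched, which is an as-treated analysis. The label hides this from a reader who sees only the name.

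The two groups are then no longer those that randomisation formed. The recoded control group gains schools that could not get a scheme running. The recoded intervention group gains schools whose parents or others pressed for one. If either trait is related to diet, memory or behaviour, the comparison mixes that relation with the effect of the scheme.

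This is also the only analysis the article describes that addresses the effect of actually running a scheme, and it is planned for all variables. Its result may be read as an effectiveness estimate.

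**Working it through.** **1. Reproducing the stated groups.** Inputs: 56 control and 55 intervention schools (abstract); 5 control schools that set up and 10 intervention schools that did not (Participation rates and school attrition).

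- Recoded control: 56 − 5 + 10 = 61. Recoded intervention: 55 − 10 + 5 = 50. Both match the article.
- Excluding the departing schools instead: 56 − 5 = 51 and 55 − 10 = 45, 96 in total.
- Schools that change arm: 15/111 = 13.5%. Of the 61, 10 (16.4%) were randomised to intervention; of the 50, 5 (10%) were randomised to control.

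**2. Contrast in set-up under randomisation.** 45/55 − 5/56 = 0.818 − 0.089 = 0.729. A complier-average estimate divides the intention-to-treat effect by this: 1/0.729 = 1.37.

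**3. Possible bias with no true effect.** Randomisation gives both arms the same expected mix of schools: 5/56 = 8.9% that would set up regardless and 10/55 = 18.2% that would not set up regardless.

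- Set-up-regardless share of the recoded intervention group: (5 + 0.089 × 55)/50 = 0.198.
- Never-set-up share of the recoded control group: (10 + 0.182 × 56)/61 = 0.331.
- Between-school standard deviation at the article's intra-cluster correlation: √0.02 = 0.141 pupil SD.

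If never-set-up schools lie d below the rest and set-up-regardless schools lie d above, the unadjusted bias is (0.198 + 0.331) × d. The documents give no value for d or its direction, so both are assumptions.

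**4. Allowing for baseline adjustment.** Table 1 gives (2205 + 2145)/111 = 39 pupils per school at baseline, say 40. The reliability of a school's baseline mean is then 0.02/(0.02 + 0.98/40) = 0.45, so adjustment removes only about half of a stable school difference. Null trials of 111 schools were simulated with the baseline school mean as covariate. Runs differed in pupils per school (40 or 50) and in how stable school effects were between sweeps, hence the ranges.

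| Assumed gap (between-school SD) | Unadjusted bias (pupil SD) | Baseline-adjusted rejection at nominal 5% |
|---|---|---|
| None | 0 | about 5% by design |
| 1 SD, both groups, same direction | 0.529 × 0.141 = 0.075 | about 16 to 24% |
| 0.5 SD, both groups, same direction | 0.529 × 0.071 = 0.037 | about 8 to 13% |
| 1 SD, never-set-up schools only | 0.331 × 0.141 = 0.047 | about 10 to 13% |
| 1 SD, both groups worse (biases offset) | (0.331 − 0.198) × 0.141 = 0.019 | about 6 to 7% |

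The adjusted bias in the second row is about 0.038 to 0.048. The adjusted intention-to-treat test stayed near 5% throughout.

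**5. Scale.** With 50 responses per school the design effect is 1 + 49 × 0.02 = 1.98, and the detectable effect is 2.80 × √(1.98/2800 + 1.98/2750) = 0.106, which rounds to the article's 0.11. An adjusted bias of 0.038 to 0.048 is 36 to 45% of that.

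**The case against.** The strongest reply is that the primary inference is sound and nothing is concealed. Intention to treat comes first for every outcome, no school withdrew, and the article openly states the recoding rule, the crossover counts and the resulting groups. That stands, and it limits the severity.

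A second reply is that adjustment for baseline and strata would carry over to this analysis. The article states the model for the primary analysis only, but changes nothing except the school coding for the secondary one, so carrying it over is the natural reading. A reader who simulates the one-SD case without covariates gets about 42 to 45% rejection and might take that as the false-positive rate. The documents do not support this, because it omits the planned adjustment; the table above therefore uses adjusted figures. Stratum adjustment was not simulated and could lower them further, but it cannot be relied on to remove differences in unmeasured school factors.

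Third, the article gives reasons for crossover but no direction of association with outcome. That also stands, and is why the offsetting case is shown.

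A reader might also infer that the coding contradicts itself over time, because the rule refers to set-up before outcome measurement while only one split, 61 and 50, is reported. The documents do not show this. The split is a count over the 12-month follow-up, and nothing says that it will be applied to the 4-month data.

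**Conclusion.** The concern holds, as a should-fix. By the article's own counts, the analysis is as-treated and mislabelled. Its susceptibility to confounding follows from the stated reasons for crossover, although an actual association between those reasons and the outcomes is plausible, not demonstrated.

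The size of the bias is unknown. With no true effect, an intra-cluster correlation of 0.02 and same-direction gaps of 0.5 to 1 between-school SD, the baseline-adjusted test rejects roughly 10 to 24% of the time. The most favourable half-SD runs fall to about 8%, and offsetting gaps leave it at 6 to 7%. The intention-to-treat result does not depend on any of this.

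**What to change.** Keep intention to treat as primary. Replace the 61-versus-50 comparison with a school-level complier-average effect: two-stage least squares with randomised allocation as instrument for set-up, the same weights and covariates as the primary model, and set-up status defined separately at each follow-up. At 12 months the estimate will be about 1.37 times the intention-to-treat effect.

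State its assumptions: allocation affects outcomes only through a scheme being set up (exclusion restriction), and no school would set up only if allocated to control (monotonicity).

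If the recoded comparison is kept, call it as-treated and non-randomised, and draw no effectiveness conclusion from it. Merely dropping the 15 schools (51 versus 45) would correct the label, but the comparison would still be non-randomised.

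The cost is a change of wording and one further model per outcome, with a wider interval than the as-treated analysis gives. No new data are needed beyond each school's set-up status at each follow-up, which the existing coding rule already requires.

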### Process evaluation

Whilst recognising the need to adopt appropriate research designs and to draw on theoretically informed outcome measures to evaluate complex interventions, it is of equal importance to understand processes [45]. The evaluation therefore incorporated a substantial process element that examined how the initiative had been implemented. This will facilitate the interpretation of outcome effects and add to the understanding of how a major policy initiative is undertaken.

An initial preliminary process evaluation was also completed with schools who began provision of free breakfasts during the first wave roll out in September 2004. This consisted of telephone interviews with the Welsh Assembly Government breakfast team, LEA co-ordinators and questionnaires with school based co-ordinators. In addition, a number of case study schools were selected for an in-depth observational and interview study with teachers, caterers and students. This preliminary study allowed process measures and an appropriate design to be developed and piloted before the main process evaluation was undertaken. Results also formed the basis of a report to the Welsh Assembly Government on the initial implementation with recommendations for policy and practice [46].

The main process evaluation consisted of telephone interviews with LEA co-ordinators, a postal questionnaire for school co-ordinators of the scheme and interviews and observation in case study schools. Following lessons learnt from the preliminary study, the process evaluation drew on the framework proposed by Steckler and Linnan [47] to examine the following areas:

1. Context. Existing dietary health promotion activity to determine the relationship between school climate, implementation and outcomes [48].

2. Fidelity and dose. Details of initiative content and a comparison of daily record keeping for the Assembly Government and for guidance documentation.

3. Integration. Details of existing, and any changes to, school policies and the level of integration with curriculum and extra-curricular activities.

4. Recruitment, participation and reach. Approaches to promotion and recruitment, any use of targeted recruitment, level of, and explanation for, participation and non participation.

5. Implementation and sustainability. Barriers and facilitators to implementation, level and type of staff involvement, level and type of parental involvement, in and out of school time involved, direct and indirect financial costs, benefits and costs to school, staff, students and parents.

The case study schools consisted of eight participating schools from each phase of the evaluation that were purposefully selected to explore these issues in greater depth. Schools were chosen so that differences in size of school, local education authority, setting (e.g. urban or rural) and percentage of free school meal entitlement were reflected. School selection was determined by information gathered from the teachers, uptake records and school characteristics. In this way a range of approaches to, and experiences of, implementation were examined. In these schools, semi-structured interviews were conducted with head teachers, teachers, breakfast scheme staff and students attending the scheme. The interviews asked for accounts of any changes to the school, dietary behaviour, school behaviour, attitudes and norms as well as views on, and experiences of, the initiative and its implementation. Breakfast schemes were observed in each of the case study schools with observational records taken of the delivery of the intervention.

Finally a questionnaire was sent to head teachers in all participating schools asking about policies, initiatives and contextual issues that had occurred over the course of collecting the quantitative data. In this way, events that may have affected the outcome data could also be taken account of.

### Participation rates and school attrition

Of the schools where baseline data were collected, no schools withdrew from the study prior to final data collection. There were however five schools randomised to the control group who nevertheless set up a free breakfast scheme prior to the 12-month follow up, while ten schools randomised to the intervention group had not set up the scheme within the follow-up period. Thus the per protocol analyses have 61 schools coded as control schools and 50 as intervention.

#### Participation of students

Response rates for students participating in classroom data collections are presented in Table 1. Whilst there was some minor variation between measures in terms of responses, with for example some children arriving late in class having missed one measure or having to leave before the final measure had been completed, these differences were negligible. Response rates for cognitive testing ranged from 85.5 to 87.9%, for the attitudes measure from 86.3 to 88.3% and for the dietary recall questionnaire from 86.2 to 88.4%. For ease of reading, detailed response data relating to only the attitudes towards breakfast questionnaire are presented, with the choice of measure entirely arbitrary.

**Table 1 T1:** Response rates and reasons for non-participation amongst students within control and intervention schools, at baseline, 4-month and 12-month follow up

	Intervention			Control		
	
	DC1	DC2	DC3	DC1	DC2	DC3
Sampled	2484	2533	2569	2442	2437	2493
Parent refusal	12	0	2	6	0	0
Left school	9	34	60	11	20	41
Eligible	2463	2499	2507	2425	2417	2452
Data collected	2205	2201	2272	2145	2157	2200
Data missing/invalid	18	13	5	14	8	31
Excluded due to special educational needs	37	19	11	23	16	7
Child refusal	3	0	2	3	6	7
Absent	200	266	217	228	230	205
Class unavailable on day of testing	0	0	0	12	0	0

For both control and intervention schools, and across all 3 data sweeps, data were collected from more than 85% of those eligible to take part, with the majority of non-participation due to the child's absence from the school on the day of testing. Only very small numbers of children were excluded either by parents prior to data collections or by their decision not to give consent on the day of testing. The variation between the numbers of children sampled at each sweep reflects the clustered nature of the sampling strategy, with repeated cross sections sampled from within each school, varying marginally from one time point to the next due to changing class compositions.

The flow of participants through the study is presented in Figure 2. The inflow and outflow of participants between the first and 12 month follow ups reflects the fact that the follow-up of each school at 12 months is in effect a repeated cross-section design from the perspective of students. Thus, approximately half of the cohort recruited for the baseline and first follow-up measures are replaced at 12 months by an incoming group of year 5 students. These repeated cross-sections will be used for school-level analyses which are the primary analyses for the trial. Additional research questions may be addressed through analysis of the nested cohort of participants eligible to participate at all 3 time points, of whom there were 1975 who provided data at baseline and one or both of the follow-ups.

**Figure 2 F2:**
[figure not shown]
Flow of participants through the study.

## Discussion

### Key issues in conducting the evaluation

A number of key issues arising from this, and similar, evaluations are likely to be of interest to those attempting to undertake similar work. Developing and maintaining an effective working relationship with schools is crucial to a project involving such long-term commitment and intrusion into their operation. Related to this, efforts to minimise attrition rates are crucial. Further potential difficulties arising from attempting to align a research timetable with an externally defined policy timetable include response biases and contamination. A number of ethical and operational issues surround gaining consent from students and parents and the undertaking of data collections in primary schools settings.

### Working with schools to conduct research

It is important to remember that schools' involvement in a large-scale trial such as this requires significant voluntary co-operation and commitment from a group of professionals with many conflicting demands and priorities. The trial of the Primary School Free Breakfast Initiative required both a considerable relinquishment by schools of control over when to set up the initiative, and a commitment to participate for a period of over one year. Given these concerns, the importance of maintaining a positive working relationship with schools is paramount. Principles for maintaining such relationships are laid out by Peterson et al [49], including maintaining regular contact and keeping schools up to date with relevant information, minimising the burden of work for schools, responding to the needs of the school and expressing gratitude for participation (p.154).

These principles were followed throughout this trial from recruitment onwards. Once the schools expressed an interest in taking part, a research team member visited the school and discussed any concerns that they may have, before the head teacher either agreed to set up the scheme or withdrew interest. This meeting was intended to ensure that schools were fully informed and aware of their commitments as participants, as well as providing an opportunity to address any concerns. Some considerable work on the part of the schools was required, in terms of for example completing questionnaires and twice labelling 35 parental questionnaires with addresses (as we could not ask for these addresses ourselves due to data protection restrictions). Hence, it was important to make clear from the outset exactly what was expected, and that the payment for taking part was our way of expressing gratitude for this dedication.

This visit, from the research team member who would be leading data collections in that school, helped to humanise the project, providing the school with a contact person for any concerns regarding the study. Where possible, this contact remained constant throughout, though in many cases this was not possible due to staff turnover. For schools wishing to participate, contact details were provided for an LEA representative to speak to about operational issues surrounding the scheme. Over the course of the following year, the research team maintained regular contact with schools, sending newsletters to keep schools up to date with the trial's progress and thanking them for their involvement.

